### Qualitative data analysis

Qualitative data will be analyzed using QSR NVivo 8 (Qualitative Solutions and Research, Pty Ltd, Victoria, Australia), a software program for managing, coding, analyzing, and retrieving qualitative data. Data will be coded electronically in NVivo 8 and printed out by code, reviewed for accuracy, and examined for links to other codes. This “axial coding” [95] process will connect code categories and identify relationships between codes which are suggestive of themes. Furthermore, as part of the ongoing analytic process, comparing and contrasting themes within and across the two strata (“constant comparison method”) will detect similarities and differences in the data [95]. Verbatim quotes will be selected to validate researchers’ coding and interpretations. The Z test and Student’s *t* test will be used for continuous variables satisfying normality assumption, and Mann Whitney *U* test and Kruskal-Wallis Test will be applied for variables which cannot satisfy the normal assumption. All statistical comparison tests will be at a 95 % significance level.

### Safety monitoring

Study procedures and participants will be monitored throughout the course of the project to ensure patient safety and minimal risk. Intervention and study coordinators will monitor study participants at consent, all data collection encounters, and during intervention activities for any discomfort, satisfaction with study participation, and for any questions or concerns participants may have. At critical data collection junctures, the PI will review the data set to ensure de-identification prior to analysis. On a daily basis, the PI and Biostatistician will ensure the security of all data files. The National Institute of Arthritis And Musculoskeletal And Skin Diseases (NIAMS)-appointed Safety Officer (SO), [name], along with the Data and Safety Monitoring Committee (DSMC), which will consist of Doctors [name], [name], and [name], will review safety and study conduct information on a semi-annual basis or on an ad hoc basis should safety or privacy concerns be raised. NIAMS determines the frequency of safety reports that are submitted to the Safety Officer. The frequency is most often bi-annually. The report is submitted to KAI Research, Inc. (KAI) and KAI will then inform NIAMS and the SO that it is available for their review.

Any adverse events (AE) or serious adverse events (SAE) will be communicated to the USC IRB. AEs will be collected during each follow-up phone call by prompting participants to let the Intervention Coordinator and/or GA know if they have experienced any AE. In addition, should events be reported in-between follow-up calls, those will be recorded immediately. The PI will be notified of all AEs and SAEs. All SAEs will be reported to the independent SO through KAI and NIAMS within 48 h of the PI becoming aware of the event.

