### Adherence assessment

In addition to quarterly review of their IIP, intervention participants will receive biweekly follow up calls to gauge their progress, comfort, adherence, and occurrence of any adverse events. In addition to enrollment in a local CDSMP, participants in the set menu control arm will receive monthly follow up calls to gauge their progress, comfort, adherence, and occurrence of any adverse events. Set menu controls will complete post-intervention follow-up evaluations bi-annually. Participants in the control arm will not receive follow-up calls, but will complete post-intervention follow-up evaluations on the same schedule as set menu controls. At their second post-intervention follow-up evaluation (after one year), set menu controls and controls will be invited to participate in the intervention activities of the program and have the opportunity to create their own IIP with the same options that were originally extended to intervention participants. From then, all participants will review their plan with the intervention coordinator on a quarterly basis, at which time measures will be repeated and each participant will be invited to change and/or add options to their plan. All participants will then receive monthly follow up calls to gauge their progress, comfort, adherence, and occurrence of any adverse events.

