### Outcomes assessments

Study assessments will be completed at baseline, 6 months, 12 months, 18 months, with a final evaluation at 24 months, for a total of five assessments. All patients who have agreed to participate will be mailed questionnaires for completion and compensation upon return, along with return postage and instructions for completing instruments. A randomly selected sub-sample (*n* = 50) of interested patients will be invited for assessment of urine catecholamine levels and urine collection instructions will be included in their mailed materials at baseline and 24 months/final evaluation. Mailed assessments will include: The Arthritis Self-Efficacy Scale, the Personal Health Questionnaire Depression Scale (PHQ-9), the Lupus Quality of Life Questionnaire (LUP-QOL), the Systemic Lupus Activity Questionnaire (SLAQ), and the Stanford Patient Education Research Center Questionnaires assessing medical outcomes such as hospital visits, illness intrusiveness, and use of stress management techniques.

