### Primary outcome

We expect the proposed study to demonstrate that a unique intervention strategy can reduce disease activity and damage, as well as perceived and biological indicators of stress, while improving quality of life indicators in African-American lupus patients. This will result in changes (a) health behaviors (use of stress management techniques), (b) health status (quality of life, depression, perceived psychosocial stress, and disease activity), (c) health care utilization (hospitalizations, emergency room visits, and communication with physicians) and (d) biological markers (urinary catecholamines).

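### Usual-care controls get no adverse-event calls in year 1, and the questionnaires that record their hospitalisations are not named as a source of serious adverse events

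*Protocol article*

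**What the plan says.** **How events are collected.** Under Safety monitoring, adverse events are gathered at each follow-up call by "prompting participants to let the Intervention Coordinator and/or GA know if they have experienced any AE" (GA is the graduate assistant). For anything else, "should events be reported in-between follow-up calls, those will be recorded immediately". Coordinators also watch for problems in person: "Intervention and study coordinators will monitor study participants at consent, all data collection encounters, and during intervention activities for any discomfort".

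**Who is called.** Under Adherence assessment, "intervention participants will receive biweekly follow up calls to gauge their progress, comfort, adherence, and occurrence of any adverse events". The set menu arm is called monthly with the same questions. The usual-care arm is not called until the one-year evaluation, after which all participants are called monthly.

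**What the questionnaires hold.** Outcomes assessments sets evaluations at baseline and at 6, 12, 18 and 24 months: "All patients who have agreed to participate will be mailed questionnaires for completion and compensation upon return". Self-report measures also allows telephone administration. The outcomes include "health care utilization (hospitalizations, emergency room visits, and communication with physicians". The lupus activity questionnaire (Disease indices) also asks about seizures and stroke. No section names a returned questionnaire as a source of adverse events.

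**How events travel upward.** "The PI will be notified of all AEs and SAEs". No time is attached to that step. The limit that is stated reads "All SAEs will be reported to the independent SO through KAI and NIAMS within 48 h of the PI becoming aware of the event".

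**What the counts are for.** Safety monitoring lists total SAEs, counts of one type of SAE and rising event frequency among the findings that may suspend enrolment or intervention. It has events reviewed by group.

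**The concern.** If the collection rule is followed exactly, a control-arm admission in year 1 enters the safety record only if the participant volunteers it. The trial will nevertheless ask that participant about hospital use at 6 and 12 months and keep the answer as outcome data.

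Two things are at stake. First, the total SAE count that may trigger a pause can be too low because of events the trial already holds. Second, the by-group review compares arms asked about events at very different frequencies. The comparator is asked least, so a difference in SAE counts could reflect calling rather than harm, and the two called arms could look worse than they are. Year 1 is also the period that the Data analytic plan uses for the primary outcomes, so a mismatch between the hospitalisation outcome and the SAE log would fall in the main comparison.

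The start of the 48-hour clock is a smaller matter. Staff who take the calls learn of an event before the PI does, and a slow hand-off would not breach the stated limit.

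**Working it through.** The 48 hours is a procedural limit, so there is no plan figure to reproduce. The check sets the schedules side by side and then sizes the gap.

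**Inputs from the protocol article:** 50 participants per arm (Study design); call frequencies (Adherence assessment); six-monthly evaluations (Outcomes assessments). **Assumptions:** biweekly means every two weeks; events fall uniformly between contacts; 0.1 to 0.5 hospitalisations per patient-year, a range the article neither gives nor supports; hospitalisation counts as serious, since the article prints no SAE definition.

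**Step 1: wait until the next scheduled contact.** Longest wait = contact interval; mean wait = interval / 2.

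| Arm and period | Scheduled contact | Longest wait | Mean wait |
|---|---|---|---|
| Intervention, year 1 | call every 2 weeks | about 14 days | about 7 days |
| Set menu, year 1 | monthly call | about 30 days | about 15 days |
| Usual care, year 1 | 6-monthly questionnaire | about 182 days | about 91 days |
| All arms after month 12 | monthly call | about 30 days | about 15 days |

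The usual-care row excludes the time taken to return the form. Randomization also provides one courtesy call to controls, but its purpose is to tell them their allocation and when to expect contact.

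**Step 2: scheduled adverse-event prompts per participant in year 1.** Intervention 52 / 2 = 26; set menu 12; usual care 0.

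**Step 3: size of the period without prompts.**
- Patient-years: 50 x 1 = 50, out of 150 x 2 = 300 in the trial, or one sixth.
- Forms: 50 x 2 (months 6 and 12) = 100.

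**Step 4: events in that period.** Expected hospitalisations = 50 x rate, so 50 x 0.1 = 5 and 50 x 0.5 = 25. If a share v is volunteered, the number missing from the SAE log is 50 x rate x (1 - v). The 5 to 25 is therefore the ceiling, reached at v = 0.

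**Step 5: effect on the review.** At equal true rates, each arm expects the same 5 to 25 in year 1. In the extreme case where calls find every event and no control volunteers one, the log shows 5 to 25 in each called arm and 0 in usual care. The year-1 total is then short by 50 / 150, one third. The article gives no numerical threshold for a pause, so the effect on that decision cannot be computed.

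**Step 6: the clock.** Total delay = wait to contact + staff-to-PI time + up to 48 hours. The middle term has no stated limit. Starting the clock at first staff awareness bounds it but leaves the first term, which is the large one in usual care, unchanged.

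**The case against.** The strongest reply is that the chain does end with the PI. The sentence just before the 48-hour limit says that the PI is told of every event, and volunteered events are recorded at once. A staff-to-PI limit and a form-screening procedure are operational details that an article may leave to the full protocol. Questionnaires may be done by telephone, and coordinators monitor all data collection encounters. Data are entered promptly and the PI has access to the identifiers, so coding would not prevent anyone tracing an event. The programme is a voluntary educational one, described as minimal risk.

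Much of this stands. The untimed hand-off alone would be a minor note, and a telephone-administered questionnaire might well bring an event to a coordinator's attention. The reply does not answer the main point, because the article does state its collection rule and its call schedule. Together they leave one arm unprompted for a year. A form returned by post is not plainly an encounter at which a coordinator observes anyone.

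A reader might infer more: that serious events in any arm can lie for months before the clock starts, or that all 150 x 4 = 600 post-baseline forms and 300 patient-years (30 to 150 events at the same assumed rates) lack a route to the SAE count. The documents do not support that. The other 300 - 50 = 250 patient-years have prompts every two weeks or monthly. A wait of months follows from the schedule only for usual care in year 1, and there it comes from the absence of calls, not from whose awareness starts the clock.

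**Conclusion.** The point holds for the usual-care arm in year 1: about 50 patient-years and 100 questionnaires with no prompted adverse-event collection and no stated route from a reported hospitalisation to the SAE count. That is up to about 5 to 25 hospitalisations, conditional on the assumed rates, on hospitalisation meeting the trial's SAE definition and on none being volunteered. Any volunteered report lowers the figure. The bias in the by-group review runs towards undercounting the comparator; its actual size cannot be known from the article.

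That the outcome table and the SAE log will disagree is possible but not shown. The seizure and stroke items are self-rated symptoms and cannot be taken as SAEs without review. The 48-hour clock is a secondary weakness. The correction is worth making because it is cheap and the counts feed the safety review.

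**What to change.** Reconcile Adherence assessment, Outcomes assessments and Primary outcome with Safety monitoring:

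1. Name returned questionnaires, on paper, electronic or by telephone, as a source of adverse events and SAEs in all arms.
2. Screen each form on receipt for hospitalisations and other events that meet the trial's SAE definition, and pass them to the PI as SAEs.
3. Reconcile questionnaire hospitalisations with the SAE log before each semi-annual report, and state the call frequency by arm beside any by-group table.
4. Start the 48 hours when any study staff member first learns of the event.

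Items 1 to 3 close the missing route; item 4 closes the untimed hand-off. None shortens the wait of up to about six months before a control completes a form, and the report should say so.

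The cost is a few changed sentences and a brief check at data entry on at most 150 x 4 = 600 six-monthly forms, plus any quarterly repeat measures. There will also be more SAE reports, many of them expected lupus admissions.

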## Discussion

Results from this trial will provide important insight into the design and effectiveness of a culturally sensitive educational intervention which includes self-selection of program components aiming to improve quality of life and health status among African American patients with lupus. We have built on three decades of empirical work conducted in the field of arthritis self-management, but differs in that the intervention mode, the disease (lupus), and the study population (African Americans) are unstudied or understudied. This psycho/educational intervention is unique in that it will be a la carte. It will allow each participant to choose which mode or modes by which they care to participate. These modes include small group, mail, and/or listserv discussion group. Such a culturally sensitive educational intervention which includes self-selection of program components has the potential to improve disparate trends in quality of life, disease activity and depression, and stress among African American lupus patients, as better self-management outcomes have been documented when participants are able to choose/dictate the content and/or pace of the respective treatment/intervention program [68–71]. Since there is currently no “gold standard” self-management program specifically for SLE, the IQAN project may have a considerable impact on future research and policy decisions. Since this proposal addresses a health disparities need in the field of lupus, wide-spread implementation in urban communities that have large populations of underserved minorities who would benefit from such an interventions is an attainable goal.

### Trial status

Currently, 153 participants have been randomized and 30 have completed all assessments.

## Abbreviations

ACR, American College of Rheumatology; AFSHP, Arthritis Foundation Self-Help Program; ASMP, arthritis self-management program; CBSM, cognitive-behavioral stress management; CD, compact disc; CDSMP, Chronic Disease Self-Management Program; CNS, central nervous system; DNA, deoxyribonucleic acid; DSMC, Data and Safety Monitoring Committee; EBPP, Evidence based prevention program; FACIT-F, functional assessment of chronic illness therapy-fatigue; FDA, Food and Drug Administration; GA, graduate assistant; HCl, hydrogen chloride; IIP, individualized intervention plan; IQAN, intervention to improve quality of life for african-american lupus patients; IRB, Institutional Review Board; KAI, KAI Research, Inc.; LC/MS-MS, liquid chromatography/tandem mass spectrometry; LFA, Lupus Foundation of America; LUP-QOL, lupus quality of life questionnaire; MOS, medical outcomes study; MUSC, Medical University of South Carolina; NIA, National Institute on Aging; NIAMS, National Institute of Arthritis and Musculoskeletal and Skin Diseases; NRS, numerical rating scale; NSAIDS, Non-steroidal anti-inflammatory drugs; OHRP, Office for Human Research Protections; PGA, patient global assessment; PHQ-9, personal health questionnaire depression scale; PI, Principal Investigator; RE-AIM, reach, effectiveness, adoption, implementation, and maintenance; RNA, ribonucleic acid; SCDHEC, South Carolina Department of Health and Environmental Control; SCLGOA, South Carolina Lieutenant Governor's Office Administration; SF-36, short form 36 health survey; SLAM, systemic lupus activity measure; SLAQ, systemic lupus activity questionnaire; SLE, systemic lupus erythematosus; SLEIGH, SLE in Gullah health; SO, safety officer; UC, usual care; USC, University of South Carolina
